**9.3.2. Analysis for secondary outcome**

The incidence of injection pain for each group will appear as a relative risk with 95% CIs and will be compared using Fisher’s exact test.

Maximum blood pressure after tracheal intubation, the number of vasopressors used, the dose of drugs used for anesthesia induction, and the time from the start of sedative drug administration to loss of consciousness will appear median with interquartile ranges and will be tested using Student’s t-test or Mann–Whitney U test.

Logistic regression analysis will be performed using body mass index, sex, age, ASA physical status, Charlson comorbidity index, clinical frailty scale, preinduction hypertension, hypertension in the ward, use of antihypertensive drugs, use of sleep-inducing drugs, serum albumin level, and types of anesthesia induction drugs to explore the factors associated with the incidence of hypotension during the induction of general anesthesia.

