**6.2. Sample size**

Ninety cases (standard treatment group: 45 cases and trial drug group: 45 cases)

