**6.5. Treatment plan**

**6.5.1. Protocol treatment**

**6.5.1.1. Trial drug group**

Remimazolam (12 mg/kg/h) will be continuously infused using a syringe pump until loss of consciousness, and then sevoflurane 1.5% will be started for maintenance of anesthesia. Three minutes after loss of consciousness, tracheal intubation was performed using a McGRATH MAC video laryngoscope.

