**6.5.1.2. Control group**

Propofol (0.25 mg/kg/10 s) will be continuously infused using a syringe pump until loss of consciousness, and then sevoflurane 1.5% will be started as maintenance of anesthesia. Three minutes after loss of consciousness, tracheal intubation will be performed using a McGRATH MAC video laryngoscope.

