**8.2. Secondary outcome**

- - 1. Maximum MBP 3 min after tracheal intubation
    2. Minimum heart rate after loss of consciousness.
    3. The number or dose of any type of vasopressor between the start of sedative administration and 3 min after tracheal intubation
    4. The time from the start of sedative drug administration to loss of consciousness. The loss of consciousness is defined as the loss of both the response to verbal stimuli and the reflex of the eyelashes. Loss of response to verbal stimuli was confirmed by calling his/her name every 10 s from the start of sedative drug administration.
    5. The dose of drugs used for anesthesia induction (*i.e.*, propofol or remimazolam)
    6. Incidence of injection pain. Participants will be asked a question about pain on injection after the start of sedative drug administration.

Pain on injection will be estimated by the following four-point scale:

0 = no pain

1 = mild pain (pain reported only in response to questioning and without any behavioral signs)

2 = moderate pain (pain reported in response to questioning and accompanied by a behavioral sign, or pain reported spontaneously without questioning)

3 = severe pain (strong vocal response or response accompanied by facial grimacing, drawing back the arm, or tears).

- - 1. Characteristics of the participants (age, sex, height, weight, medical history, comorbidity, medications [antihypertensive drugs, sleep-inducing drugs, antipsychotics, and central nervous system agents], ASA physical status, clinical frailty scale, surgery procedure, laboratory values of the latest surgery [hemoglobin, creatinine, and serum albumin]).
    2. Exploring factors associated with the incidence of hypotension

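### The planned between-arm test of induction dose compares milligrams of two different drugs, so its p-value mainly reflects the infusion rates and mg potency

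*Protocol*

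**What the plan says.** Section 8.2 of the protocol lists among the secondary outcomes "The dose of drugs used for anesthesia induction", and adds in brackets that this means propofol or remimazolam. It is therefore the study drug itself, not a co-medication that both arms share.

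Section 9.3.2 places this dose in the same list as maximum blood pressure after intubation, vasopressor use and time to loss of consciousness. The list closes with "the dose of drugs used for anesthesia induction, and the time from the start of sedative drug administration to loss of consciousness", and all of these variables "will appear median with interquartile ranges and will be tested using Student’s t-test or Mann–Whitney U test".

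The two treatment sections fix how the dose arises:

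- Section 6.5.1.1: "Remimazolam (12 mg/kg/h) will be continuously infused using a syringe pump until loss of consciousness".
- Section 6.5.1.2: "Propofol (0.25 mg/kg/10 s) will be continuously infused using a syringe pump until loss of consciousness".

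The protocol states no hypothesis for the dose comparison and no conversion between the two drugs.

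**The concern.** A two-group test needs a variable that means the same thing in both groups. Here the variable is milligrams of propofol in one arm and milligrams of remimazolam in the other. A milligram of one is not a milligram of the other in effect, so equality of the two doses is not a hypothesis anyone would hold, and rejecting it teaches nothing about the drugs.

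At stake is a secondary result that is likely to be reported as statistically significant and could be read as a finding, for example that one drug needs a smaller dose, when it largely restates the infusion rates written into the protocol. An SAP that follows the protocol would inherit the test, because Section 9.3.2 states it outright and does not leave it open.

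**Working it through.** The plan gives no figure of its own for this comparison, so there is nothing to reproduce. The check is what the test would measure.

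**Inputs from the protocol**

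- Remimazolam rate (Section 6.5.1.1): 12 mg/kg/h.
- Propofol rate (Section 6.5.1.2): 0.25 mg/kg per 10 s.
- Group size (Section 6.2): 45 per arm.

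**Step 1: rates in one unit**

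- Remimazolam: 12 / 60 = 0.2 mg/kg/min.
- Propofol: 0.25 × 6 = 1.5 mg/kg/min.
- Ratio: 1.5 / 0.2 = 7.5.

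**Step 2: dose as a function of time**

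With a constant rate that stops at loss of consciousness, dose per kg = rate × time. If both arms took 60 s, the doses would be 0.2 × 1 = 0.2 mg/kg and 1.5 × 1 = 1.5 mg/kg. At any common time they differ 7.5-fold.

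**Step 3: where the null hypothesis lies**

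Equal mg/kg means 0.2 × T(remimazolam) = 1.5 × T(propofol), that is T(remimazolam) = 7.5 × T(propofol). Dividing every dose by 0.2 leaves the ranks unchanged, so a Mann-Whitney test on mg/kg is the same as a Mann-Whitney test of remimazolam times against propofol times multiplied by 7.5. It is the time comparison with its null moved to a place that nobody chose.

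**Step 4: how often the test would reject**

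The protocol gives no expected induction times, so these are assumed: log-normal times, propofol median 60 s, coefficient of variation (CV) 0.3 or 0.5, 42 analysed per arm (slightly below the 45 planned), 2,000 simulated trials, two-sided 5%. Ranges run over the two CVs and, for dose, over both tests. Time was tested with Mann-Whitney only.

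| Remimazolam time / propofol time | Dose test rejects | Time test rejects |
| --- | --- | --- |
| 1 | 100% | 3.8% to 5.7% |
| 1.5 | 100% | 96% to 100% |
| 2 | 100% | 100% |
| 3 | 100% | 100% |
| 5 | 95% to 100% | 100% |
| 7.5 | 4.6% to 4.9% | 100% |

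The first and last rows show the problem. When induction times are identical, the dose test always rejects. When remimazolam takes 7.5 times as long, the dose test rejects at about its nominal 5%, while the time test always detects the difference.

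**The case against.** The strongest reply is that this is one of several secondary outcomes. No decision rule or conclusion hangs on it, and the primary outcome, sample size and safety analysis do not use it. A reader who sees milligrams of two different drugs is unlikely to be misled. This stands, and it is why the point is minor.

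Three stronger readings are tempting, and the documents do not support them.

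- *The p-value reflects potency and infusion rate only.* It does not: dose per kg is rate times time to loss of consciousness, so it also carries patient response. That component is real, but the protocol already tests it separately.
- *A significant result is guaranteed.* The protocol gives no induction times. The near-certain rejection above depends on the assumed median and spread, and it disappears if remimazolam induction takes about 7.5 times as long.
- *The rest of the sentence is also wrong, because it pairs medians with a possible t-test and leaves the choice of test open.* Naming two candidate tests in the protocol and leaving the choice to the SAP is ordinary practice, and the SAP is not at hand. The sentence does not require a t-test for any variable.

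A reader might also want a Hodges-Lehmann difference for the vasopressor count, expecting many zeros. On the planning figures in Section 9.2 (40% hypotension under propofol, relative risk 0.28, hence 0.40 × 0.28 = 11.2% under remimazolam), and if vasopressors are given only for hypotension, about 0.60 × 0.888 = 53% of between-arm pairs would be zero against zero. At most 40% could have the propofol count higher. The median pairwise difference would then be 0 even with a real effect, so that change is not recommended.

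**Conclusion.** The concern holds for induction dose alone. Section 9.3.2 states a between-arm test of a variable that has no common scale across the arms. The 7.5-fold rate difference follows from the protocol by arithmetic. It puts the null of equal mg/kg at a 7.5-fold difference in induction time, assuming a constant rate that stops at loss of consciousness as Sections 6.5.1.1 and 6.5.1.2 describe. The rejection rates rest on the assumed times and are illustrative; the lack of a meaningful null does not depend on them.

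This is a wrongly stated analysis rather than a missing detail, but a minor one. The point concerns only how the dose is analysed and takes no position on the infusion rates themselves.

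**What to change.** In Section 9.3.2, remove the induction dose from the variables to be tested. State instead that it will be reported descriptively by arm in mg/kg, as median and interquartile range, with no between-arm p-value. Keep it as a recorded outcome in Section 8.2. Time to loss of consciousness, measured in the same units in both arms and already on the tested list, then carries the between-arm comparison.

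The cost is a wording change and the loss of one uninterpretable secondary p-value. Data collection, sample size and trial conduct do not change.

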**6.5.2.3. Treatments that can be used in combination**

**Hypotension**

a) Hypotension with heart rate <80 beats/min, ephedrine 4 mg

b) Hypotension with heart rate ≥80 beats/min, phenylephrine 0.05 mg.

**Bradycardia** (heart rate <45 beats/min)

a) Bradycardia without severe hypotension, atropine 0.5 mg bolus (one additional dose allowed.)

b) Bradycardia with hypotension and ephedrine 4 mg is acceptable in addition to atropine.

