**9.2. Calculation of sample size**

The frequency of hypotension associated with the induction of general anesthesia was estimated to be 40% based on cases similar to our protocol extracted from our institutional data for a randomly selected month. In a previous study, the relative risk of remimazolam to propofol for the frequency of hypotension associated with induction of anesthesia was reported to be 0.28. If Fisher’s exact probability test with a type I error set at 5% and a power greater than 80% will be performed, it was estimated that at least 84 participants per group would be needed. Considering a dropout, we decided to include 45 participants in each group (*i.e.*, 90 in total).

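### Vasopressor use is summarised only by a median with IQR, which at the plan's own rates usually gives a median of 0 in both arms and no usable effect size; add the proportion treated (minor)

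*Protocol*

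**What the plan says.** Protocol section 8.2 lists as a secondary outcome "The number or dose of any type of vasopressor between the start of sedative administration and 3 min after tracheal intubation". Section 7.2.5 collects the same item.

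Section 9.3.2 carries only the number of vasopressors into the analysis. It is grouped with blood pressure, induction dose and time to loss of consciousness. All four "will appear median with interquartile ranges" and are tested by Student's t-test or the Mann-Whitney U test. No effect estimate is named for any of them. In the same section, injection pain does get one: a relative risk with a 95% CI.

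Section 6.5.2.3 ties the drugs to hypotension, choosing the agent by heart rate. The first entry reads "Hypotension with heart rate <80 beats/min, ephedrine 4 mg"; the second gives phenylephrine at higher heart rates. Ephedrine appears again for bradycardia accompanied by hypotension.

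The rates come from section 9.2: "The frequency of hypotension associated with the induction of general anesthesia was estimated to be 40" per cent, and "the relative risk of remimazolam to propofol for the frequency of hypotension associated with induction of anesthesia was reported to be 0.28".

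**The concern.** A count that is 0 for most participants is poorly described by its median. If fewer than half of each arm receive a vasopressor, both medians are 0 whatever the difference between the arms. Section 9.2 places both arms below one half.

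The need for a vasopressor is the treatment-side counterpart of the primary outcome, and readers will want to know how much it changed. A p-value beside two medians of 0 does not tell them. The estimate that usually accompanies a rank test, the Hodges-Lehmann shift, has the same weakness, because most pairwise differences between the arms are ties at 0 or are offset by such ties.

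The outcome wording adds a small ambiguity. Section 8.2 says number or dose, while section 9.3.2 analyses number only.

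**Working it through.** **Inputs.** Control rate 0.40 and relative risk 0.28 (section 9.2), so the remimazolam rate is 0.40 × 0.28 = 0.112. Planned size: "we decided to include 45 participants in each group". Error rates: "with a type I error set at 5% and a power greater than 80" per cent; a two-sided test is assumed.

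**Are these the rates behind the sample size?** Let p1 = 0.40, p2 = 0.112, d = 0.288 and p̄ = 0.256.

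- Uncorrected: n = [1.96·√(2·0.256·0.744) + 0.842·√(0.24 + 0.0995)]² / 0.288² = (1.210 + 0.490)² / 0.0829 ≈ 34.8, so 35 per group.
- With continuity correction: (34.8/4)·[1 + √(1 + 4/(34.8·0.288))]² ≈ 41.5, so 42 per group and 84 in total.
- Exact Fisher power is 83.3% at 42 per group and 85.0% at 45.

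The printed "at least 84 participants per group would be needed" does not reproduce as a per-group figure, since power there would be about 99%. As a total it reproduces exactly and fits the planned 90. That is a separate point. Here it shows that 40% and 11.2% are the working rates.

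**Median.** Assume that a participant receives a vasopressor exactly when hypotensive. Expected users among 45 are 45 × 0.40 = 18 and 45 × 0.112 ≈ 5, a difference of 28.8 percentage points. With 45 participants the median is the 23rd ordered value, which is 0 if there are at most 22 users.

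- Propofol: P(Bin(45, 0.40) ≤ 22) = 0.914.
- Remimazolam: P(Bin(45, 0.112) ≤ 22) > 0.9999.
- Both medians 0: about 91% (about 88% with 42 per arm).

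**Upper quartile.** With 45 participants this is the 34th ordered value, above 0 if there are at least 12 users.

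- Propofol above 0: P(Bin(45, 0.40) ≥ 12) = 0.978.
- Remimazolam equal to 0: P(Bin(45, 0.112) ≤ 11) = 0.997.
- Both together: 0.978 × 0.997 ≈ 0.975.

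The usual report is therefore 0 (0 to at least 1) versus 0 (0 to 0).

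**Test and shift estimate.** The documents give no distribution of doses per treated participant. It was simulated as 1 + Poisson(m), with m = 0, 0.5 or 1; this is an assumption. At 45 per arm, Mann-Whitney power is about 88 to 90%. The Hodges-Lehmann shift is exactly 0 in about 96 to 99% of trials across 42 to 45 per arm.

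**Dependence on the rates.** At the 60% versus 33% cited in section 2.3, P(Bin(45, 0.60) ≤ 22) = 0.086, so the propofol median would usually be above 0. Both medians would be 0 in only about 9% of trials.

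**The case against.** A reader might infer that this endpoint cannot show a treatment effect. The documents do not support that. The IQR is reported with the median and would separate the arms in about 97.5% of trials, and inference rests on a named test with power close to that of the primary analysis.

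The rates can also be disputed. The zero median depends on 40%, and the only rates in the protocol for hypotension that needed treatment are 60% versus 33%, at which the problem largely disappears. Those describe a whole anaesthetic, however, whereas this outcome covers induction, the period to which the 40% refers. For the same reason, the absence of a directly comparable proportion adds little to the case.

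A sharper objection is that the premise weakens the remedy. If vasopressor use matches hypotension exactly, the proportion treated repeats the primary outcome, which already gets an odds ratio (section 9.3.1.1) and a risk difference (section 9.3.1.2). If it does not match, the proportion is new information but the 91% loses its exact basis. Section 6.5.2.3 gives no numeric trigger, so the match is an assumption. This stands as a reason to rate the point as minor. It does not make the median a good summary, because the vasopressor outcome would still lack an effect size of its own.

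Finally, the number-or-dose wording does little harm. Section 9.3.2 picks number, and nothing in the protocol plans to add milligrams of two different drugs.

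**Conclusion.** The point holds as a minor weakness in reporting. Section 9.3.2 gives a zero-heavy count a median and IQR and no effect estimate. At the section 9.2 rates, with 45 per arm, both medians would be 0 in about 91% of trials while the share treated differs by 28.8 percentage points. A difference can be detected, with Mann-Whitney power of about 89%, but its size would not be reported in usable form.

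This rests on three assumptions: vasopressor use follows hypotension, the control rate is near 40%, and, for the power and shift figures only, the simulated dose counts are reasonable. The reading that the endpoint fails is not supported. Neither the primary outcome nor its analysis is touched.

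**What to change.** - In section 9.3.2, keep the planned rank test for the number of vasopressors. Add the proportion of participants given at least one vasopressor between the start of the sedative and 3 min after intubation. Report it with the Mantel-Haenszel risk difference and 95% CI that section 9.3.1.2 already specifies for the primary outcome.
- Show the number of boluses per participant as a frequency table by arm.
- In section 8.2, state that number is the analysed outcome, and report ephedrine and phenylephrine doses separately.

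The data are already collected under section 7.2.5, so the cost is wording plus one further secondary analysis. That analysis partly overlaps the primary outcome and should be presented as supportive. No treatment rule changes.

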**7.2.2. Pre-induction of general anesthesia**

(1) Vital signs

Before starting preoxygenation, NIBP and heart rate were measured twice as baseline vital signs.

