**9.3. Statistical methods**

**9.3.1. Analysis for primary outcome**

**9.3.1.1. Main analysis**

The incidence of hypotension in the intervention and control groups will be calculated. The odds ratio (OR) with 95% confidence intervals (CIs) between both groups was calculated. The incidence of hypotension between the two groups will be compared using the Mantel−Haenszel χ^2^ test and adjusted OR for the stratification factor for randomization. Homogeneity across strata will be assessed using the Breslow-Day test.

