**9.3.1.2. Additional analysis for primary outcome**

**1) Subgroups for analysis:** The subgroup for analysis will be generated as the following factors:

- 1. Charlson comorbidity index ≤2 or ≥3
  2. Clinical frailty scale ≤4 or ≥5
  3. Hypertension in the ward the day before surgery is defined as SBP ≥140 mmHg or diastolic blood pressure ≥90 mmHg
  4. Age (<90 or ≥90 years old)

The proportion of people aged ≥90 years in the total Japanese population is 2.1% (approximately 2.61 million), which is significantly different from the 12.8% (approximately 16.19 million) of people in their 80s. This was determined based on the assumption that this group is particularly affected by adverse drug reactions and circulatory instability.

**2) Sensitivity analysis of the primary analysis:** The OR with 95% CI adjusted for preinduction blood pressure (SBP ≥160 mmHg or <160 mmHg) will be calculated using the Mantel−Haenszel χ^2^ test. This cut-off point for SBP was as follows: (1) calculated based on the median value in the historical data of our institution for similar age groups; (2) and was determined regarding the exclusion criteria for blood pressure in a previous study on the efficacy and safety of remimazolam.

**3) The absolute risk reduction values with 95% CI** adjusted for stratification will be calculated using Mantel−Haenszel risk differences.

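### The protocol compares maximum MBP after intubation without its measured pre-induction baseline or the randomisation stratum: a valid test, but less precise than the collected data allow

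*Protocol*

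**What the plan says.** Protocol 8.2 lists "Maximum MBP 3 min after tracheal intubation" first among the secondary outcomes. Section 9.3.2 groups it, as maximum blood pressure, with vasopressor number, induction dose and time to loss of consciousness. It says that these outcomes "will appear median with interquartile ranges and will be tested using Student’s t-test or Mann–Whitney U test". Neither a covariate nor a stratum is named.

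The baseline of the same quantity is collected. Section 7.2.2 reads: "Before starting preoxygenation, NIBP and heart rate were measured twice as baseline vital signs". Exclusion criterion 14 in 5.2 turns on mean pressure before induction, so that value has to be known for each analysed participant.

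Elsewhere the protocol treats earlier pressure as prognostic:

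- Section 6.4.4 stratifies allocation by ward hypertension, on the ground that usual pressure bears on pressure after induction.
- Section 9.3.1.1 has the primary outcome "compared using the Mantel−Haenszel χ^2^ test and adjusted OR for the stratification factor for randomization".
- Section 9.3.1.2 adds a sensitivity analysis for the primary outcome: "The OR with 95% CI adjusted for preinduction blood pressure (SBP ≥160 mmHg or <160 mmHg) will be calculated".
- The exploratory logistic model for hypotension in 9.3.2 includes preinduction hypertension and ward hypertension.

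**The concern.** A post-intubation pressure usually varies between patients partly because their resting pressures differ. A two-sample test leaves that part of the spread in the error term, whereas an analysis that conditions on the baseline removes it. The binary primary outcome gets a stratum adjustment and, as a sensitivity analysis, a dichotomised pre-induction pressure. The outcome that is itself a continuous pressure gets neither.

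At stake is the width of the confidence interval, and with it the chance of detecting a real difference between the drugs in the highest pressure after intubation. The trial is sized for the primary outcome, so precision on this outcome is whatever 45 per arm happens to give. A baseline that is already recorded is the cheapest way to improve it.

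**Working it through.** **Inputs.** From the protocol: 45 per group (6.2 and 9.2) and a type I error of 5% (9.2, primary outcome; taken here as two-sided). Assumed, because the protocol gives neither: the correlation ρ between mean pre-induction MBP and the outcome, varied from 0.2 to 0.7, and an unadjusted power of 80%.

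**Is there a figure of the plan's own to reproduce?** Not for this outcome. The only calculation, in 9.2, concerns the primary outcome, "with a type I error set at 5% and a power greater than 80% will be performed". Its inputs (40% and a relative risk of 0.28, so 0.40 × 0.28 = 11.2%) give 42 per group with continuity correction, that is 84 in total. The text says 84 per group. That is a separate matter and does not enter below.

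**Step 1: variance.** Conditioning on a baseline with correlation ρ multiplies the residual variance by 1 − ρ². At ρ = 0.5 this is 1 − 0.25 = 0.75, a 25% reduction. The standard error is multiplied by √0.75 = 0.866, so the interval is about 13% narrower.

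**Step 2: equivalent sample size.** An unadjusted test needs 90 / (1 − ρ²) participants to match an adjusted one with 90. At ρ = 0.5 this is 90 / 0.75 = 120. This step needs no assumed power.

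**Step 3: power.** In the normal approximation, 80% unadjusted power at 45 per arm corresponds to d = (1.960 + 0.842) × √(2/45) = 0.591 SD. Adjusted power is Φ(2.802 / √(1 − ρ²) − 1.960). At ρ = 0.5 this is Φ(3.235 − 1.960) = Φ(1.275) = 89.9%.

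| ρ (assumed) | 1 − ρ² | Unadjusted N matching 90 | Power, from 80% | Gain (points) |
|---|---|---|---|---|
| 0.2 | 0.96 | 93.8 | 81.6% | 1.6 |
| 0.3 | 0.91 | 98.9 | 83.6% | 3.6 |
| 0.4 | 0.84 | 107.1 | 86.4% | 6.4 |
| 0.5 | 0.75 | 120.0 | 89.9% | 9.9 |
| 0.6 | 0.64 | 140.6 | 93.8% | 13.8 |
| 0.7 | 0.51 | 176.5 | 97.5% | 17.5 |

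**Step 4: checks.** The non-central t distribution at the same d, with one degree of freedom removed for the baseline, gives 79.1% unadjusted, 82.7% at ρ = 0.3, 89.2% at 0.5 and 93.4% at 0.6, so the gains are nearly the same. The starting power also matters. At ρ = 0.5 the gain is 11.9 points from 50%, 12.4 from 60%, 11.8 from 70%, 9.9 from 80% and 6.3 from 90%.

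**Step 5: two readings.** Averaging two baseline readings that correlate r with each other raises ρ to ρ × √(2 / (1 + r)). A single-reading ρ of 0.50 becomes 0.513 at r = 0.9 and 0.542 at r = 0.7. The benefit is small but free.

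**The case against.** The strongest reply is that nothing here is wrong. Randomisation makes the unadjusted comparison unbiased, and its type I error already allows for chance imbalance at baseline. Stratifying by ward hypertension limits imbalance in resting pressure further. All of that stands. A reader might infer that imbalance in resting pressure biases the planned comparison. It does not: it is ordinary sampling error, which adjustment reduces.

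The second reply is that the correlation may be low. Between the awake readings and the post-intubation maximum come remifentanil, the study drug, sevoflurane, laryngoscopy and vasopressors given for low pressure (6.5.1 and 6.5.2). Excluding pre-induction mean pressure below 70 mmHg narrows the range of the covariate. This also stands, and it is why the lower rows of the range deserve as much attention as ρ = 0.5. It does not remove the case for adjustment: with 90 − 2 = 88 error degrees of freedom, a weak covariate costs next to nothing.

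Third, this is one of several unpowered secondary outcomes, and a statistical analysis plan that is not at hand may settle covariates and effect estimates. The first part is right and limits the importance of the point. On the second, the absence of a stated effect estimate is not counted as a fault here. The test itself, however, is named in the protocol and so can be reviewed.

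**Conclusion.** The point holds as an optional gain in efficiency. It is not an error in the plan, and the primary result does not depend on it.

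Its size is conditional. With ρ between 0.2 and 0.7 and 80% unadjusted power at 45 per arm, both assumed, adjustment adds about 2 to 18 points of power. A reader might take the 10 points at ρ = 0.5 as the loss built into the plan. The protocol supports neither the correlation nor the starting power behind that figure, and the drugs given between baseline and outcome make a smaller gain plausible. The calculation credits the baseline alone; any further gain from the stratum has not been estimated.

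What rests on the document and not on assumption is that the named test uses no covariate, that the outcome's own baseline is recorded twice, and that the protocol itself regards earlier pressure as prognostic.

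**What to change.** In 9.3.2, name the outcome as maximum MBP after intubation, in line with 8.2, and state whether the maximum is taken over the one-minute readings of 7.2.5. Analyse it by ANCOVA with three terms: treatment, the mean of the two pre-induction MBP readings as a continuous covariate, and the hypertension stratum used at randomisation. Report the adjusted mean difference with its 95% CI. Keep medians and interquartile ranges as description, and keep a rank-based test as a sensitivity analysis if the residuals are clearly skewed.

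This takes a sentence or two in 9.3.2, to be fixed before the allocation is revealed. It needs no new measurement or visit. The statistical cost is about one degree of freedom per covariate, so the error degrees of freedom go from 88 to 86 with both terms in the model.

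### The exploratory logistic regression in 9.3.2 lists 12 predictors for about 23 expected events, so odds ratios of real factors will be exaggerated unless the fit is penalised

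*Protocol*

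**What the plan says.** Protocol 8.2 closes its list of secondary outcomes with "Exploring factors associated with the incidence of hypotension". Protocol 9.3.2 gives the method: "Logistic regression analysis will be performed using body mass index, sex, age, ASA physical status, Charlson comorbidity index, clinical frailty scale, preinduction hypertension", followed by ward hypertension, antihypertensive use, hypnotic use, serum albumin and the induction drug. That makes 12 predictors. ASA classes I to III are eligible (5.1), so there are 13 parameters if ASA is entered as categories. The section mentions no variable selection, penalisation or limit on model size.

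The expected number of events follows from 9.2. The control rate "was estimated to be 40% based on cases similar to our protocol extracted from our institutional data for a randomly selected month", and "the relative risk of remimazolam to propofol for the frequency of hypotension associated with induction of anesthesia was reported to be 0.28". Enrolment is 45 per group, 90 in total (6.2 and 9.2).

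**The concern.** Maximum-likelihood logistic regression is biased away from the null when the number of parameters is large relative to the rarer outcome. Here 12 or 13 parameters share about 23 events. Several factors also overlap: three concern blood pressure (ward hypertension, pre-induction hypertension, antihypertensive use) and three concern general health (ASA class, Charlson index, frailty scale).

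Identifying factors is the only purpose of this model. Exaggerated odds ratios for real factors, and widely scattered ones for irrelevant factors, would defeat that purpose. The model also contains the randomised drug, so it produces a second, covariate-adjusted drug odds ratio for the primary endpoint. That estimate is expected to look more favourable than the truth.

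**Working it through.** **1. The plan's own sample-size figure.** The inputs are 40% against 0.28 × 40% = 11.2%, type I error 5% (taken as two-sided) and power above 80%. The usual two-proportion formula is

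n = [1.96·√(2·p̄·q̄) + 0.842·√(p₁q₁ + p₂q₂)]² / (p₁ − p₂)², with p̄ = 0.256.

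This gives (1.96 × 0.617 + 0.842 × 0.583)² / 0.288² ≈ 34.8, so 35 per group, or 42 with continuity correction. Exact two-sided Fisher power is 0.833 at 42, 0.850 at 45 and 0.990 at 84 per group. The 84 stated per group in 9.2 therefore reproduces only as a total (2 × 42), which fits the 90 enrolled. That discrepancy is a separate matter. The event count below uses 45 per group.

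**2. Expected events.**
- 45 per group: 45 × 0.40 + 45 × 0.112 = 18.0 + 5.04 = 23.04. Divided by 12 this is 1.92 per predictor; divided by 13 it is 1.77 per parameter.
- 42 evaluable per group: 16.8 + 4.7 = 21.5, or 1.79 per predictor.
- No drug effect, 40% in both groups: 36 events, or 3.0 per predictor.
- Ceiling at any incidence: 45 events and 45 non-events, 45/12 = 3.75.

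The model is therefore large for 90 patients whatever the true rates.

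**3. Size of the bias.** The true drug odds ratio is (0.112/0.888)/(0.40/0.60) = 0.189, with log −1.665. The simulation used 2,000 trials per setting, the drug plus 11 factors with no effect, and unpenalised maximum likelihood with all 12 entered. Because the other factors have no effect, the true adjusted and unadjusted odds ratios coincide, so any excess is bias.

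| Setting | Mean log OR | Overstatement | Median OR |
|---|---|---|---|
| 45 per group, factors uncorrelated | −2.101 | 26% | 0.133 |
| 45 per group, correlation 0.2 | −2.105 | 26% | 0.127 |
| 42 per group, correlation 0.2 | −2.193 | 32% | 0.123 |
| 45 per group, drug only (uncorrelated setting) | −1.744 | 5% | 0.177 |

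Further runs at 45 per group with other covariate prevalences and correlations gave overstatements between 21% and 30%. Most of the excess comes from model size, since the drug-only model is off by about 5%.

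**4. Factors with no effect.** At 45 per group each reaches p<0.05 in 6.1–6.3% of trials by Wald test and 7.5–7.9% by likelihood ratio. At least one of the 11 does so in 46–47% (Wald) or 53–55% (likelihood ratio) of trials. The benchmark for 11 independent tests at an exact 5% is 1 − 0.95¹¹ = 43%, so overfitting adds roughly 3 to 12 percentage points. A binary factor with no effect has a median apparent odds ratio of about 1.6 (or its inverse), and one in ten exceeds about 3.4–3.6.

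**5. Fits that fail.** The rate depends on how common the binary factors are. It was about 0.5% in the runs above (1.6% at 42 per group) and 0.2–1.4% with prevalences of 20–50%. It rose to 26–35% when a few factors had prevalences of 8–15% and any coefficient beyond 8 on the log-odds scale counted as diverged.

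**6. Firth's penalty, same predictors.** The bias in the drug log odds ratio falls to within about 2%, and its standard deviation falls from about 0.8 to about 0.6.

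**The case against.** The strongest reply is that this is a labelled exploration on which nothing depends. Sections 8.2 and 9.3.2 both describe it as exploring factors, it stands last in the list of outcomes, and no prediction score or decision rests on it. The drug effect comes from the stratified Mantel-Haenszel analysis in 9.3.1. All of this stands and limits the weight of the point.

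A second reply is that 9.3.2 does not say that all factors enter at once or how the model is fitted, and that an analysis plan not shown here may settle both. This stands in part. The absence of a penalty is not in itself an error in a protocol. But the protocol does fix the list of 12, joint entry is the plain reading, and the number of predictors relative to events is the source of the difficulty.

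Two stronger readings are tempting. A reader might infer that irrelevant factors will generally pass as risk factors. They will not: each does so only about 5–8% of the time, and the roughly even chance of at least one false lead is mostly the 43% that any 11 unadjusted tests would give. A reader might also infer that a substantial share of fits will break down. The protocol gives no covariate prevalences, so anything from under 1% to about 30% is possible and no single figure can be defended.

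**Conclusion.** The point holds as a limited one. Under the protocol's own assumptions the model has under 2 events per predictor. Fitted in the ordinary way with all factors together, it is expected to exaggerate real effects; for the drug this is about 20–30% on the log scale at 45 per group (median odds ratio about 0.13 against 0.19). About half of such trials would flag at least one factor with no effect, mainly through multiple testing.

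The event counts and the 3.75 ceiling rest only on the protocol's figures. The simulated sizes also rest on joint entry, maximum likelihood, and assumed covariate distributions and correlations. Nothing here supports the inference that the trial's drug effect is compromised: the primary result does not use this model. The change is worth making because it is cheap and the bias is avoidable.

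**What to change.** In 9.3.2, state that the logistic regression is fitted with Firth's penalised likelihood, and that its estimates are reported as exploratory with no adjustment for multiple testing. Any separate analysis plan should carry the same wording.

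The cost is analysis wording only, with no extra patients or data. The downside is that estimates are shrunk and fewer factors will reach nominal significance. The penalty does not remove the multiple-testing component, which is why the exploratory label must accompany the results. Shortening the predictor list, for instance among the overlapping blood-pressure and health-status factors, is optional and a matter of preference.
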